### Implementation science framework and applications

HOPE-inG applies implementation science methods to facilitate the adoption of HOPE’s evidence-based components into Ghana's healthcare system. The goal is to enhance the adoption, fidelity, and sustainability of these interventions, ensuring they are effectively embedded within existing health infrastructure and are responsive to local context and needs.

We have selected the Exploration, Preparation, Implementation, and Sustainment (EPIS) implementation science framework [47, 48] to guide this project. EPIS is a combined determinant-process framework that is phased and multilevel and guides evidence-based interventions' planning and implementation process. Key constructs of EPIS are (1) the EBI(s), (2) Bridging factors, (3) Outer context, and (4) Inner contexts. EPIS focuses on identifying and leveraging bridging factors that connect the Outer and Inner contexts and is useful in guiding EBI implementation towards established practice in different settings, including in LMICs [48, 49] (Fig. 1.)

**Fig. 1 Fig1:**
[figure not shown]
Conceptual framework for HOPE intervention implementation

#### Bridging factors and implementation support strategies

Bridging factors are formal relationships and processes that exist between the Inner organizational context and the Outer policy/funding system context [50]. Bridging factors are complex but critical driving forces for EBI implementation and sustainment [50]. This proposal aims to translate the HOPE EBI into practice, and implementation strategies that specifically leverage bridging factors to achieve adoption, scale-up, and sustainment will be highly relevant. For the HOPE-inG study, we refer to implementation strategies that specifically leverage bridging factors as “implementation support strategies” (ISS), given that implementation support is technical and logistical assistance in implementing evidence-informed practices, policies, and programs, and in sustaining and scaling evidence for population impact [51]. (Fig. 1). In other words, HOPE-inG’s ISS will facilitate the routinization and integration of the HOPE EBI into practice by leveraging bridging factors that connect the Inner organizational and Outer funding/policy contexts.

#### The outer and inner contexts

The HOPE-inG Outer Context consists of policymakers (Ministry of Health, Ghana Health Services, National AIDS and Sexually Transmitted Infection Control Program (NACP)) and their policies (e.g., cervical screening, treatment, and insurance policies) (Fig. 1). The Ministry of Health formulates health policy and sets standards for healthcare. The Ghana Health Service oversees day-to-day health services and implements health policies. The NACP provides care and support services for persons with HIV. The Inner Context embodies the organizational clinic setting (study sites) and consists of clinicians implementing HOPE (e.g., physicians and nurses), supporting staff (e.g., patient navigators), and health facility administrative staff.

### Formative study in Preparation Phase

We conducted a formative study to identify barriers and facilitators to implementing and scaling up the HOPE intervention in Ghana’s health system. The findings informed the selection of potentially high-impact and feasible ISS. We used a nominal group technique (mixed methods) and the Consolidated Framework for Implementation Research (CFIR, qualitative) [52] to rapidly collect and organize data on barriers and facilitators from a total of 65 people in four nominal groups: WLWH (intervention recipients; *n* = 16), healthcare workers (intervention deliverers; *n* = 16), health facility managers (*n* = 16), and government officials (*n* = 17) (decision-makers). Participants generated their ideas individually and then shared and clarified them with the group in a round robin fashion. Thereafter, all ideas were ranked according to frequency, feasibility, and health system priority.

Here, we briefly report the formative study findings. The top three to five determinants from each nominal group were then collated into a priority list. A total of 29 highly ranked determinants (13 facilitators, 16 barriers) were identified across all five CFIR domains: Inner Setting (12), Outer Setting (6), Implementation Process (6), Innovation (2), and Individuals (4). These determinants were then matched to 73 implementation strategies from the Expert Recommendations for Implementing Change (ERIC) that were deemed feasible [53]. Out of the 73 matched implementation strategies, 24 were identified as ISS and relevant to implementation support in the Inner Setting and at the interface of the Inner and Outer Setting.

We used Lengnick-Hall et al.’s bridging factor “form and function” dimensions [50] to highlight key bridging factors and ISS identified for local implementation of the HOPE intervention, and ISS identified from the nominal groups that address these key bridging factors (Table 1).

**Table 1 Tab1:** Prioritized bridging factors and implementation support strategies for HOPE implementation

Bridging Factor	Type	Capital Exchanged	Proposed Implementation Support Strategy	Impact on Inner and/or Outer Context
Advisory interactions between management and government health officials	Relational tie	Technical support from officials to management	Support program for clinic management to include government advice	Improved health facility management support and implementation climate for providers implementing HOPE
Government-approved policies and delivery modalities for screening and treatment	Process	Clinical and logistical guidance for providers' implementation of HOPE	Healthcare provider support and capacity building	Improved provider knowledge and self-efficacy in delivering HOPE. Pathway to sustained and structured HOPE implementation
Inter-agency collaboration in guiding and refining HOPE implementation	Relational tie	Social capital, sources of power involvement, existing infrastructure and resource alignment	Multiagency representation (e.g., SAB) for HOPE implementation	Synergy in government policy, existing resources and infrastructure for sustainable HOPE implementation at facilities
Government role in social network support for HOPE implementers	Relational tie Process	Implementation experiences Moral and technical support	WhatsApp^©^ group to foster social network support for providers implementing HOPE	Ongoing government, clinical (from Teaching Hospital) and peer support for providers implementing HOPE. Better insight into challenges and opportunities
Contribution of government/facility vs patient funding in HOPE intervention	Formal arrangement	Money	Discuss expectations and decision-making on funding arrangements for HOPE in SAB	Government and facility-level clarity, expectations set and concrete information shared on HOPE funding and degree of integration into routine care

Inner setting: health facility; Outer setting: government agencies, funding, policies, and procedures

Additional bridging factors may be identified, and ISS will be reviewed and refined during study implementation

At the end of the formative study, a ten-member Stakeholder Advisory Board (SAB) was convened among nominal group participants, comprising WLWH, healthcare providers, clinical managers, and policymakers. The Board provides high-level technical and contextual expertise in designing and implementing the intervention and in disseminating findings to the broader body of stakeholders in Ghana.

### Site selection

The proposed research will be conducted in the Central Region, home to approximately 2.8 million people [54] and has the fifth-highest HIV burden among Ghana’s 16 regions [55]. We will leverage established partnerships with HIV clinics in the Central Region and with the National AIDS/STI Control Program (NACP) to select secondary-level facilities with similar infrastructure. In the Central Region, 85 antiretroviral therapy (ART) clinics operate across 22 districts. The selection criteria included: a clinic that is the largest district-level hub site, has highly accessible spokes, and has enrolled at least 400 WLWH on ART. The largest hub sites that have already established access to cervical cancer screening and treatment services at a tertiary referral facility were excluded. A master list of study-eligible women was developed through the existing HIV E-tracker electronic medical record system. Ultimately, four study sites were selected for randomization for the intervention arm (two sites: Our Lady of Grace Hospital, Breman Asikuma and Saltpond Municipal Hospital, Mfantseman) and the control arm (two sites: Saint Francis Xavier Hospital, Assin Fosu and Swedru Government Hospital, Agona West). 

The combined workforce across the selected sites includes approximately 500 staff and a total bed capacity of over 700. For project implementation, we will engage existing personnel, including health facility administrators, clinicians (doctors, nurses, midwives), and support staff (including patient navigators), collectively referred to as “healthcare providers”.

### Study Preparation, Implementation and Sustainment Phases

We have completed the Exploration Phase, where we evaluated cervical screening needs and the fit of the HOPE intervention in Ghana. Through prior efficacy, formative, and effectiveness studies, we identified WLWH and healthcare workers' needs for cervical screening [23, 35, 56, 57], which guided our development and evaluation plan for HOPE. HOPE-inG thus focuses on EPIS’ remaining three phases for the five-year study period:Preparation Phase (Year 1): relevant to Aim 1, where we identified potential barriers and facilitators of HOPE implementation and developed a health system implementation plan and provider’s training content for HOPE implementation. This phase has been completed.Implementation Phase (Years 2 and 3): relevant to Aim 2, where we assess the effectiveness of the HOPE 2.0 intervention and the success of the implementation plan.Sustainment Phase (Years 3–5): relevant to Aim 3, where we assess the impact of the implementation plan on the sustainment of HOPE 2.0 implementation at study sites.

Study design, population, analysis, and outcome measures are described per study phase.

### Preparation phase

To develop a culturally appropriate, evidence-based implementation plan and provider training materials to support the effective delivery of the HOPE 2.0 intervention within Ghana’s health system.

#### Design

We are applying an explanatory sequential mixed methods design to develop and refine a plan for integrating the HOPE 2.0 intervention into Ghana’s existing health system. We have already completed the nominal groups for this phase, with identification of determinants, relevant implementation strategies, and ISS, as described above. The next steps will be to apply these formative findings to modify HOPE to HOPE 2.0, along with the development of a HOPE 2.0 health system implementation plan and provider implementation training materials relevant to the plan.

#### Study population

Besides the 65 participants from the nominal groups already described, we plan to purposively select and survey 10 providers from each study site (total *N* = 40). This pre-implementation baseline survey will focus on implementation outcomes of feasibility, acceptability, and appropriateness of the HOPE 2.0 implementation plan (including HOPE 2.0 and ISS), using the psychometric scales developed by Weiner et al. [58] Findings from this survey will be used to refine the implementation plan.

#### Outcome measures and analysis

Nominal group analysis has already been described above. We will use descriptive statistics recommended by Weiner et al. [58] to analyze the feasibility, acceptability, and appropriateness data. These measures are brief and each takes about 5 min to complete, comprising four questions posed to the participant with responses to each question provided on a five-point Likert scale: *Completely disagree*; *Disagree; Neither agree nor disagree*; *Agree*; or *Completely agree.* Individual participant scores will be computed for each scale with a maximum score of 20 per scale (max 5 points for each of 4 questions), with the mean computed across participant groups. We will then categorize the individual scores in each participant group into tertiles, as high, middle, and low scores for each scale.

### Implementation phase

Assess the effectiveness of the HOPE 2.0 intervention and the success of the implementation plan in a hybrid type 2 trial.

*Hypothesis: Cervical screening uptake by HPVSS will be significantly higher among WLWH in the intervention vs. the control group, and implementation outcomes scores among intervention group providers will be significantly higher than those of control group providers.*

#### Design

We will conduct a hybrid type 2 cluster randomized controlled trial to simultaneously evaluate the effectiveness and implementation of HOPE 2.0 using bridging factor-focused ISS. HIV clinics at the four selected secondary-level facilities will be cluster randomized 1:1 in a two-arm trial. WLWH in the intervention group will receive HOPE 2.0 from providers trained and supported to implement HOPE 2.0 using ISS-focused training materials and per the implementation plan developed in the Preparation Phase. After this intensive 6 month implementation phase, technical and clinical support from the study team and clinical experts to the intervention sites will be withdrawn, after which the Sustainment Phase will begin

WLWH in the control group will also receive HOPE, from providers without ISS or an implementation plan (Table 2 and Fig. 2). At the end of this 6 months period of implementation, the study team will provide ISS materials to control group health facilities to co-implement with HOPE 2.0. There will be a similar Sustainment Phase for the control sites.

**Table 2 Tab2:** HOPE-inG baseline provider training in intervention vs control arms

	**Topic**	**Intervention Arm**	**Control Arm**
1	Epidemiology of cervical cancer (CC) in women with and without HIV	Yes	Yes
2	The WHO cervical cancer elimination agenda	Yes	Yes
3	The HOPE intervention: components and evidence	Yes	Yes
4	Cervical cancer screening strategies	Yes	Yes
5	Pre- and post cervical screening counselling	Yes	Yes
6	Psycho-social support for clients with positive cervical screening results and their immediate family	Yes	Yes
7	Awareness creation, record keeping and documentation	Yes	Yes
8	Research ethics: participant recruitment, study procedures and collecting, documenting and reporting data	Yes	Yes
9	Delivering the HOPE intervention in Ghana: Implementation research to practice	Yes	No
10	Who is supposed to do what, where and when? The HOPE 2.0 implementation plan	Yes	No
11	How will we deliver the intervention? Implementation support strategies for HOPE 2.0	Yes	No
12	What resources do we have for successful implementation? Additional tools, job aids, support and training for delivering HOPE 2.0	Yes	No

**Fig. 2 Fig2:**
[figure not shown]
Study implementation procedures and process/outcome assessment time points. WLWH: women living with HIV; ISS: implementation support strategies

#### Study population

We will recruit participants representing four organizational levels, including WLWH patients, healthcare providers, clinic managers, and policymakers.

### Inclusion and exclusion criteria and recruitment

#### Inclusion criteria

General eligibility criteria are living and/or working in the Central Region and ≥ 18 years old.Specific eligibility criteria for providers are to possess healthcare training and/or qualifications (i.e., patient navigators, physicians, nurses) and work at the HIV clinic; for clinic managers, health facility management in administrative leadership, and oversee HIV clinic operations.Study eligibility criteria for women in the trial include women who are living with HIV (regardless of pregnancy status), between 25 and 65 years old (age consistent with WHO cervical screening guidelines [2]); have never had cervical screening (Pap smear or HPV test), or have not had cervical screening in the last five years.Eligible community members include individuals (with and without HIV and/or cervical cancer) living in the study communities and/or family members of WLWH.Eligible policymakers include personnel from the National AIDS/STI Control Program, Ministry of Health, and Ghana Health Service.

#### Exclusion criteria

WLWH who have a cervix are the main target population for the HOPE-inG study. WLWH who or have had a total hysterectomy (inclusive of the cervix) will be excluded.

#### Recruitment

*Doctors, nurses, patient navigators, and clinic managers:* We will meet with Medical Directors of the selected health facilities to discuss the study and the recruitment of providers. We will recruit providers by email, phone, and face-to-face contact.*WLWH* will be recruited using E-tracker electronic records. Participating providers at each site will identify eligible women from their site-level sampling frame (400–600 per site for a total pool of ~ 3,900 WLWH) and contact them by phone to solicit participation. Verbal informed consent will be sought in English/applicable local language by research coordinators prior to trial initiation. Participant recruitment is ongoing and will be completed by March 2028.*Community members* will be recruited from study communities via community gatekeepers.Ghana Health Service and the Ministry of Health will facilitate the recruitment of government officials through written and verbal invitations and snowball recruitment.

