### Outcomes measures

The primary outcomes of interest in this type 2 hybrid trial are 1) the effectiveness of the HOPE 2.0 intervention in increasing uptake of cervical screening among WLWH, and 2) the adoption of HOPE 2.0 intervention at the facility level. Other outcomes, including cost, fidelity, penetration, and sustainability, will be assessed as secondary outcomes. Additionally, Proctor et al.’s [61] client (i.e., WLWH) health outcomes will also be assessed (Fig. 2).*Cervical screening uptake* is defined as the proportion of WLWH in each study arm that successfully complete the cervical screening process. In the intervention arm, completing the process requires the WLWH to present to the clinic, collect a self-test kit, collect a cervical sample, and submit the sample to the clinic for testing. In the control arm, completing the process requires the WLWH to present to the clinic and receive a pap smear/cervical sample collection from a provider. WLWH in either study arm who do not complete the entire process will not be considered as completing uptake. Uptake assessment will therefore be determined as proportion of WLWH with complete screening out of all women enrolled in each study arm.*Program Adoption* is defined as the decision of healthcare workers (i.e., providers and management) and patients (described as patient uptake) to commit to and use HOPE 2.0 and ISS adoption. Adoption will be measured at provider, management, and patient levels using a variety of data logs, surveys, and interviews.At the management level, we will assess (i) the number of ISS training sessions attended and (ii) the degree to which ISS components are used to support providers.At the provider level, we will assess (i) the number of ISS training sessions attended, (ii) the degree to which ISS components are used, and (iii) the number of implementation plan steps followed. Additionally, we will assess providers’ (i) implementation experience (i.e., resource availability, managerial support, and technical issues confronted); and (ii) operational experience (i.e., workload increase or decrease, flow of health facility communication, and any skills needed).*Implementation Cost* is defined as the total expenses (facility/provider and patient) for implementing HOPE 2.0. Cost will be assessed at the health facility level in both study arms. We will use a micro-costing approach to estimate the economic costs associated with each study arm. The direct measure method of micro-costing involves tracking resources used and enumerating unit costs for each resource to precisely estimate cumulative costs associated with each study arm [62]. Implementation cost will be measured at the health facility level and patient level, utilizing a variety of cost-tracking databases throughout the study period to itemize, quantify, and value resources.At the health facility level, a cost-tracking database will be used throughout the study period to itemize, quantify, and value resources. Costs at the facility level include (i) number of hours staff spent on HOPE 2.0 training; (ii) sampling materials, including kits and laboratory testing costs; (iii) recruitment (i.e., time spent identifying and contacting eligible women, advertising materials, participant incentives); (iv) HOPE 2.0 delivery (with and without ISS); and (v) treatment and biopsies.Cost to the patient will include tracking of participant out-of-pocket costs (e.g., transportation, childcare, phone data, time spent on HOPE 2.0 procedures). French et al.’s outpatient cost survey [63] (5 items) will be adapted to measure patient-level costs.Note: Time effort will be estimated using the hourly wages of WLWH and healthcare workers.*Fidelity* is the degree to which HOPE 2.0 and its ISS are implemented as planned.At the provider level, utilizing surveys, log sheets, and interviews, we will assess (i) the degree of adherence to HOPE 2.0/ISS protocols (Intervention) and HOPE 2.0 (Control) during implementation, (ii) the dose of the program delivered, and (iii) the quality of program delivery.At the management level, we will assess (i) adherence to ISS protocol (Intervention only) and (ii) overall management support for providers (both arms).We will utilize log sheets and interviews, as well as observations, and the Process Evaluation Checklist (PEC) [64] throughout to track the fidelity of implementation and overall project progress.*Program Penetration* for this proposal is the integration of HOPE 2.0/ISS within the HIV subsystem of study facility settings [61]. We will assess penetration outcomes at provider and management levels by determining the proportion of personnel who actually deliver on a HOPE 2.0 program task/role, out of the number trained or expected to deliver on that task/role.At the management level, we will utilize log sheets and interviews to measure the expected tasks or roles to be evaluated, which will be (i) the provision of technical support and (ii) facilitating a conducive HOPE 2.0 implementation climate for providers.At the provider level, we will utilize log sheets and interviews to measure the expected tasks to be evaluated, which are (i) screening and recruitment of eligible WLWH, (ii) delivery of HOPE 2.0 to enrolled WLWH, and (iii) follow-up on all testing outcomes and completion of required documentation for these tasks/roles.*Program Effectiveness* is defined as the impact of the ISS on 1) providers' self-efficacy in implementing HOPE 2.0, 2) WLWH screening uptake, and 3) treatment outcome. We will assess effectiveness outcomes at management, provider, and WLWH levels utilizing surveys, log sheets, and interviews.At the management level, we will assess (i) the frequency of support that management delivers to providers, (ii) management self-efficacy in supporting HOPE 2.0 implementation, and (iii) challenges in supporting HOPE 2.0 implementation at their facilities, utilizing log sheets and interviews.At the provider level, we will assess (i) self-efficacy for implementing HOPE, (ii) fidelity of HOPE 2.0 intervention delivery, (iii) number of WLWH screened and women with positive results who are treated, and (iv) the type, frequency, duration, and quality of service provided to patients (WLWH).At the WLWH level, we will assess the impact of HOPE 2.0 on patients’ (WLWH) screening uptake (i.e., service outcome) and receipt of screening results, patient satisfaction, and for women with positive screening results, clinical follow-up, and evaluation for, and receipt of CC treatment where appropriate (i.e., client outcomes). Assessment procedures: WLWH in both study arms will complete the screening and satisfaction outcome survey within one month of completing HOPE 2.0. Within one month of screening, providers will check the lab registry and will review the electronic medical record to confirm screening completion. Treatment compliance will be evaluated within 6 months of positive result notification. The screening and treatment completion outcomes will be binary (yes/no), test results (positive, negative, or inadequate), treatment follow-up (yes, no, or lost-to-follow-up), and patient satisfaction will be measured using a patient satisfaction survey [65].

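### Arm-aware site providers identify and phone the women after allocation, and uptake is counted only over those enrolled, so differential selection can bias the patient-level primary outcome

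*Protocol article*

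**What the plan says.** - **Who recruits.** Under Recruitment, "Participating providers at each site will identify eligible women from their site-level sampling frame", and they "contact them by phone to solicit participation". The same section says: "Verbal informed consent will be sought in English/applicable local language by research coordinators prior to trial initiation".
- **When.** The Site selection section already lists the two hospitals in each arm ("Ultimately, four study sites were selected for randomization for the intervention arm", followed by the names), and Recruitment adds: "Participant recruitment is ongoing and will be completed by March 2028". Under Study procedures, Step 1 gives intervention providers ISS and implementation-plan training. In Step 2, clinicians screen and recruit. The Control arm section has control providers follow Step 2 without ISS or plan training.
- **From what list.** Site selection says: "A master list of study-eligible women was developed through the existing HIV E-tracker electronic medical record system". No order for drawing women from it is given. Recruitment puts the frame at 400–600 women per site and about 3,900 in total.
- **The denominator.** Under Outcomes measures: "Uptake assessment will therefore be determined as proportion of WLWH with complete screening out of all women enrolled in each study arm".
- **The analysis set.** The Statistical analysis plan section specifies intent-to-treat.

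**The concern.** Randomising sites makes the arms comparable, as far as four sites can, in the women who attend them. It does not do so for the subset enrolled later by staff who know their arm. If providers in one arm more often reach, call or persuade women who are inclined to screen, the arms differ in willingness before any woman is exposed.

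Because uptake is counted over enrolled women, that difference passes straight into one of the two primary outcomes. The bias can create an apparent effect or hide a real one. Intent-to-treat preserves only the set of women enrolled, and that set is formed after allocation. Multiple imputation and complier-average analyses, planned under Anticipated challenges, do not address women who were never enrolled. The covariates listed under Quantitative data analysis are sociodemographic and clinical, and none measures willingness to screen.

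The point concerns patient-level uptake, not the facility-level adoption outcome.

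**Working it through.** The plan gives no figure for selection, so this is an illustration built on its own sizes and rates.

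**1. Inputs from the article**
- Enrolment: 288 per site, and 288 × 4 = 1,152, as stated (Sample size estimation).
- Control rate 15%, expected to rise to 30% or more, so a planned gain of 15 points (same section). The 15% is stated for adoption. Outcomes measures treats patient-level adoption as uptake, so I apply it to uptake.
- Frame: N = 400 to 600 listed women per site (Recruitment).

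**2. Room for selection**
- 288/400 = 72% and 288/600 = 48%.
- 4 × 400 = 1,600 and 4 × 600 = 2,400, which does not agree with about 3,900. The latter implies 3,900/4 = 975 per site, and 288/975 = 29.5%.

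**3. Assumptions, not in the documents**
- 15% of listed women in both arms would complete screening, so there is no true effect.
- In one arm a willing woman is r = 1.25, 1.5 or 1.8 times as likely to be enrolled as an unwilling one. The other arm enrols without selection.

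**4. Formula**

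Let W = 0.15N be the willing women and U = 0.85N the unwilling. The enrolment probabilities are s_u = 288/(rW + U) and s_w = r × s_u, capped at 1. Observed uptake = W × s_w/288. Where the cap does not bind, this equals 0.15r/(0.15r + 0.85), whatever N is.

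**5. Results with no true effect**

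| r | N = 400 | N = 500 | N = 600 |
|---|---|---|---|
| 1.25 | 18.1% | 18.1% | 18.1% |
| 1.5 | 20.8% (cap) | 20.9% | 20.9% |
| 1.8 | 20.8% (cap) | 24.1% | 24.1% |

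- r = 1.25: 0.1875/1.0375 = 18.1%.
- r = 1.5: 0.225/1.075 = 20.9%.
- r = 1.8: 0.27/1.12 = 24.1%.
- Cap at N = 400: all 60 willing women are enrolled, and 60/288 = 20.8%.

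The spurious gain runs from 18.1 − 15 = 3.1 points to 24.1 − 15 = 9.1 points. With a frame of 400 it cannot exceed 20.8 − 15 = 5.8 points.

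**6. The other direction**

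Take a true 30% in the intervention arm, with willing women there less likely to be enrolled. Observed uptake is 0.30r/(0.30r + 0.70).
- r = 1/1.25: 0.24/0.94 = 25.5%.
- r = 1/1.8: 0.167/0.867 = 19.2%.

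A true gain of 15 points over an unselected 15% control arm would then read as about 10.5 or 4 points.

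**7. Cross-check with a different model**

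Using an enrolment odds ratio of 2 for future completers against non-completers, and 15% in both arms, uptake in the selecting arm reads 17.2%, 19.5% and 21.7% at enrolment fractions of 72%, 48% and 29.5%. The bias is of the same order and grows as the enrolled fraction falls, so the frame conflict in step 2 matters here.

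**The case against.** The strongest reply is that the article describes an ordinary recruitment path with safeguards. Eligibility comes from records, and research coordinators rather than the delivering providers take consent. Providers are said to identify eligible women, not to pick among them at will. A calling order may sit in the full protocol, which is not shown. Nothing documents how a provider could recognise a future completer from a record and a phone call.

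Much of this stands as a limit on the claim. Discretionary choice of women is something a reader might infer, but the text does not state it. That providers know their arm is also an inference, since there is no blinding statement, though it is a safe one given openly arm-specific training. Neither safeguard closes the gap as described. The list defines who is eligible, not who is called, and coordinators are placed at consent while the solicitation call is the providers'. Consent before trial initiation is not the same as consent before randomisation, and recruitment continues with the arms already named. Persuasion on the phone requires no ability to predict who will screen.

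A reader might also infer that the intervention is designed to act on the denominator, because "screening and recruitment of eligible WLWH" is a provider task under penetration. The definition does not support that. Penetration is the share of personnel who perform a task, not which or how many women enter, and the minimum of 288 is the same at every site.

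**Conclusion.** The concern holds as a risk of post-allocation selection bias in patient-level uptake, in either direction. It rests on stated features: site providers identify and phone women, arm-specific training comes first, and the denominator is enrolled women only. Under assumed selection ratios of 1.25 to 1.8 and a 15% rate in both arms, the spurious gain is about 3 to 9 points against a planned 15. It is at most 5.8 points if only 400 women are listed. The ratios have no source in the article, so these figures show scale and do not forecast what will happen.

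Two stronger readings are not supported:
- Starting from 30% in both arms, the same formula gives gains of about 5 to 13.5 points (0.375/1.075 = 34.9%; 0.54/1.24 = 43.5%). But 30% is the hoped-for intervention rate, and the planned 15 points start from 15%.
- Selection alone could not produce the whole planned effect with a frame of 400. With 600 the ceiling is 90/288 = 31.3%, so reaching 30% would need nearly every willing woman enrolled (0.30 × 288 = 86.4 of 90, or 96%).

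**What to change.** - **Call order.** For all women not yet approached, have each site's E-tracker list put in random order centrally and approach women strictly in that order until the site's target is met.
- **Contact log.** Record by site the numbers listed, approached, unreachable, ineligible, declined and enrolled.
- **Sensitivity analysis.** Pre-specify uptake over all eligible women approached, using counts only, beside the analysis over enrolled women. It answers a slightly different question, since it also reflects success in recruiting, so the two should be read together.
- **Women already enrolled.** Report those enrolled before the change separately, because a random order cannot be imposed on them afterwards.
- **Frame size.** Reconcile 400–600 per site with the pool of about 3,900.
- **Residual limitation.** State that the callers still know their arm, so differential persuasion remains possible.

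The cost is one random sort per site, a simple contact log, and slightly slower recruitment because staff cannot call the easiest women first. The change is worth making now, while recruitment is open.
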